### Statistical analysis plan

The aim of the statistical analysis is to determine if there is sufficient evidence that VEN + LDAC is non-inferior to IC in terms of mEFS to warrant further research in a phase III trial and in addition that VEN + LDAC has greater benefit than IC in terms of secondary outcomes. As a non-inferiority trial, statistical analysis will be carried out on a per protocol basis which includes all patients who have received the first dose of protocol treatment. Patients who are randomised but do not receive any treatment will be replaced. Analysis will primarily focus on the ≥ 60 age group, if younger patients are recruited following the interim analysis they will be analysed as a parallel cohort.

Outcome measures will be analysed under a Bayesian framework using conjugate models with minimally informative prior distributions. For all time-to-event outcomes, the Kaplan–Meier method will be used to plot the data. The posterior probability distribution of the true log hazard ratio will be estimated using a Normal-Normal conjugate model and the hazard ratio for comparison of the treatment arms will be estimated from the exponential of the mean of this distribution together with 80% and 95% credible intervals. For the primary outcome measure of mEFS, the posterior probability that the hazard ratio (HR) is less than the non-inferiority margin of 1.29 will be reported and enable decision-making (see next section for justification of non-inferiority margin). The decision criteria for both the interim analysis and final analysis are based on there being at least 80% chance that VEN + LDAC is truly non-inferior. Thus, if the posterior probability distribution estimates that the probability of mEFS HR < 1.29 is at least 80% given the observed data and a minimally informative prior, this would be taken as a “go” decision.

For all binary outcomes that are recording the occurrence of an event, the posterior probability distributions will be estimated for the true proportion of events using a beta-binomial conjugate model and the difference in proportions will estimated together with 80% and 95% credible intervals.

Each of the eight measures contributing to cumulative resource use will be summarised individually. In addition, each resource use will be combined with unit costs and summed to give a total cost per patient. The mean total cost will be calculated for each treatment arm and the absolute difference estimated.

Quality of life, change in performance status and change in CGA will be summarised and displayed graphically.

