## Abstract

**Background:**

For patients with acute myeloid leukaemia (AML), the only potentially curative treatment is intensive chemotherapy (IC). This is highly toxic, particularly for patients > 60 years, potentially leading to prolonged hospitalisations requiring intensive supportive care, and sometimes treatment-related death. This also results in extensive healthcare costs and negatively impacts quality of life (QoL). Venetoclax with low-dose cytarabine (VEN + LDAC) is a novel, low-intensity treatment for AML patients who cannot receive IC. VEN + LDAC is given as an outpatient and toxicity appears significantly lower than with IC. Analysis of clinical trials performed to date are promising for patients with the genotype *NPM1*^mut^*FLT3* ITD^neg^, where remission and survival rates appear comparable to those achieved with IC.

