## Background

Acute myeloid leukaemia (AML) is an aggressive haematological malignancy, which despite improvements to treatment and supportive care, remains fatal in the majority of patients. The only potentially curative treatment is intensive (or induction) chemotherapy (IC) followed in selected cases by allogeneic stem cell transplantation (SCT) where indicated and when a suitable donor is identified [1, 2]. IC is successful in inducing complete remission (CR) in 60–80% of younger patients (aged 16–60 years) [3, 4] and in around 50% of older patients ≥ 60 years [5, 6]. IC is highly toxic, due mainly to prolonged myelosuppression, which results in a high risk of severe bacterial and/or fungal infection. This is the most frequent cause of induction death, which occurs in 5–10% of patients aged < 60 years [3, 4, 7] and 10–20% of older individuals [7, 8]. Patients undergoing IC are usually hospitalised for a prolonged period and require intensive support with blood products and anti-infective agents, resulting in significant economic cost (estimated a £100,000-£400,000 per patient) and impact on quality of life (QoL) [9–14]. Additionally, patients treated with IC are at risk for several serious long-term side effects including cardiac and neurological sequelae, infertility and secondary cancers [15].

As the risk of mortality with IC increases with age and comorbidity [7, 8] older patients and those with severe pre-existing conditions are typically treated with non-intensive chemotherapy with either low-dose cytarabine (LDAC) or a hypomethylating agent (HMA, i.e., 5-azacitidine or decitabine) [1, 2]. Such treatments, however, display at best modest efficacy resulting in CR in only 10–30% of patients and median overall survival rates of approximately 6–12 months [16–19]. The B-cell lymphoma-2 (BCL2) inhibitor venetoclax (VEN), has been used in combination with LDAC or a HMA in patients not eligible to receive IC. These VEN-based combinations have been shown to produce CR rates between 50–75%, representing a major advance in the treatment of AML [20–22] and leading to the approval of VEN + HMA and VEN + LDAC combination therapy for patients with AML who are ineligible for IC in many countries including the UK [23].

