### Trial outcomes

The primary outcome is molecular event-free survival time (mEFS) where an event is defined as follows:Failure to achieve morphological CR or CR with incomplete blood count recovery (CRi) after two cycles of therapy;Molecular persistence, progression or relapse requiring treatment change;Morphological relapse, or;Death.

Morphological CR is defined as < 5% blasts in a cellular bone marrow with neutrophil count ≥ 1 × 10^9^/L and platelet count ≥ 100 × 10^9^L, and CRi as < 5% blasts but with neutropenia (neutrophil count < 1 × 10^9^/L) or thrombocytopenia (platelet count < 100 × 10^9^/L) [28].

Molecular persistence is defined as detectable *NPM1* mutant transcripts present after completion of treatment with less than a 4 log_10_ reduction from baseline in the bone marrow, confirmed on a second consecutive sample; molecular progression an increase in *NPM1* mutant transcript levels by > 1 log_10_, confirmed on a second sample, and molecular relapse as detectable *NPM1* mutant transcripts, confirmed on a second consecutive sample showing an increase of > 1 log_10_ in a patient who previously tested negative in at least one technically adequate bone marrow sample (i.e., *ABL* C_t_ < 26.5 or *ABL* copy number > 10,000) [29].

Morphological relapse is defined as ≥ 5% blasts in the blood or bone marrow in a patient with a previously documented CR, CRi or morphological leukaemia free state (MLFS: < 5% bone marrow blasts, no auer rods or extramedullary disease, does not meet criteria for CR or CRi (i.e., blood count recovery is below the specified levels) [28].

Secondary outcomes include: Occurrence of morphological complete remission (CR or CRi) by the end of the second cycle of treatment; death within 30 and 60 days from trial entry; overall survival time (OS) from date of randomisation; time to morphological relapse from date of morphological complete remission; time to molecular relapse from date of molecular complete remission; cumulative occurrence of grade 3 and 4 adverse events at 12 and 24 months; prevalence of molecular complete remission at month 3, 6 and 12; cumulative resource use at 12 and 24 months including hospital admission days, blood product usage and days on intravenous antibiotics and antifungals; health-related quality of life at month 3, 6, 12, 18 and 24; change in performance status from baseline at month 3, 6, 12, 18 and 24, and; change in Comprehensive Geriatric Assessment (CGA) [30] from baseline at month 12 and 24.

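### Kaplan-Meier is prescribed for all time-to-event outcomes, including the two relapse outcomes, where death without relapse is a competing event and 1-KM overstates the proportion who relapse

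*Protocol article*

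**What the plan says.** The Statistical analysis plan section sets one method of display for every time-to-event outcome: "For all time-to-event outcomes, the Kaplan–Meier method will be used to plot the data". For the comparison of arms it continues: "The posterior probability distribution of the true log hazard ratio will be estimated using a Normal-Normal conjugate model". Neither sentence makes an exception.

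The Trial outcomes section lists among the secondary outcomes "time to morphological relapse from date of morphological complete remission; time to molecular relapse from date of molecular complete remission". Morphological relapse is defined by blast count ("Morphological relapse is defined as ≥ 5% blasts in the blood or bone marrow in a patient with a previously documented CR, CRi", with morphological leukaemia-free state also qualifying). Molecular relapse is defined by *NPM1* transcript levels. Death is in neither definition. By contrast, the event list for mEFS, the primary outcome, ends with death.

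The Statistical analysis plan section also gives the secondary outcomes a role in the conclusion. The analysis is to show non-inferiority on mEFS and "in addition that VEN + LDAC has greater benefit than IC in terms of secondary outcomes". The article mentions neither competing events nor cumulative incidence.

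**The concern.** Kaplan-Meier suits mEFS and overall survival, because death is an event in both. For an outcome whose only event is relapse, a patient who dies in remission has to be censored. The estimator then treats that patient as still able to relapse later, at the same rate as those who remain under observation. The complement of the curve no longer estimates the proportion of patients who relapse; it lies above it.

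No other absolute display of relapse is specified in the article, so a 12- or 24-month relapse percentage would naturally be read from this curve. Greater benefit on secondary outcomes is a stated aim, so a curve that overstates relapse, possibly by different amounts in the two arms, could colour that part of the conclusion.

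**Working it through.** **The plan's own figures.** The article states no figure for the relapse outcomes. Its figures concern mEFS, and they reproduce closely:

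- Margin: ln(0.55)/ln(0.63) = 1.294 (stated 1.29).
- With 116 events, the standard error of the log hazard ratio is 2/√116 = 0.186. The largest observed hazard ratio that gives a go is 1.29 × exp(−0.842 × 0.186) = 1.103 (stated critical value 1.1).
- Probability of a go at a true hazard ratio of 0.94: Φ(ln(1.29/0.94)/0.186 − 0.842) = 0.806 (stated 80%).
- Expected events from 156 patients, with exponential survival, 63% at one year in both arms, and 2 years of accrual plus 2 of follow-up: 115.6 (stated 116).

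Because mEFS counts death as an event, none of these changes under the fix.

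**Relapse outcomes: inputs.** All are assumptions, since the article gives no rate of relapse or of death in remission. Take constant hazards from the date of remission, λr for relapse and λd for death without relapse. Set them from a 2-year 1-KM relapse figure R of 20–50% and a net 2-year death figure D of 2–20%:

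- λr = −ln(1 − R)/2 and λd = −ln(1 − D)/2
- 1-KM at 2 years, deaths censored: 1 − exp(−2λr) = R
- Cumulative incidence of relapse at 2 years: λr/(λr + λd) × [1 − exp(−2(λr + λd))]

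**Worked case.** R = 40%, D = 15%. λr = 0.255 and λd = 0.081 per year. Since exp(−2(λr + λd)) = 0.60 × 0.85 = 0.51, cumulative incidence = 0.255/(0.255 + 0.081) × 0.49 = 37.2%. The overstatement is 40 − 37.2 = 2.8 points.

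**Range.**

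| R (1-KM) | D (net death) | Cumulative incidence | Overstatement, points |
|---|---|---|---|
| 20% | 2% | 19.8% | 0.2 |
| 20% | 10% | 19.0% | 1.0 |
| 40% | 5% | 39.1% | 0.9 |
| 40% | 10% | 38.1% | 1.9 |
| 40% | 15% | 37.2% | 2.8 |
| 40% | 20% | 36.2% | 3.8 |
| 50% | 20% | 45.4% | 4.6 |

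**Between arms.** With R = 40% in both arms:

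- D of 5% in one arm and 15% in the other: 2.8 − 0.9 = 1.9 points apart.
- D of 5% and 20%: 3.8 − 0.9 = 2.9 points apart.
- Equal D: 0 apart.

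Unequal relapse alone also produces a gap. With D = 10% in both arms, the overstatement is 1.0 point at R = 20% and 1.9 points at R = 40%.

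**The case against.** **It concerns only a plot.** The between-arm estimate is the log hazard ratio model, and with deaths censored that is a valid cause-specific hazard ratio. This stands. The error is confined to the curves and to percentages read from them, and the hazard ratio needs only the right label. If relapse hazards were equal, the Kaplan-Meier curves and the hazard ratio would correctly show that. Cumulative incidence answers the complementary question of how many patients actually relapse.

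**Censoring is inferred.** The article does not say how deaths are handled, and such rules are often left to the analysis plan. But the article does prescribe the method, for all such outcomes, and it defines both events without death. If death were meant to count, the outcome would be relapse-free survival and should be named so. The wording needs correcting either way.

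**Direction and size between arms.** A reader might infer that the overstatement is larger on DAGO, since the abstract says "VEN + LDAC is given as an outpatient and toxicity appears significantly lower than with IC", and that the plan therefore hides a real excess of relapse on VEN + LDAC. The documents do not support this:

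- No rate of death in remission is given for either arm. The induction deaths cited in the Background ("10–20% of older individuals") fall largely before remission, outside these outcomes.
- The Background raises equivalent or better treatment-related mortality on VEN + LDAC only as a possibility. Table 2 allows up to 12 cycles of VEN + LDAC against four of DAGO, so lower mortality in remission cannot be presumed.
- Scenarios with a large gap strain the plan's own assumption. Take relapse at 0.35 per year in both arms, with death in remission at 0.15 on DAGO and 0.05 on VEN + LDAC. At 2 years 1-KM is 50.3% in both, against cumulative incidences of 44.2% and 48.2%, so overstatements of about 6 and 2 points. But 0.35 + 0.15 = 0.50 per year on DAGO exceeds the total of −ln(0.63) = 0.46 per year implied by 63% one-year mEFS, which also has to cover induction death and failure to reach remission. If 10% die in induction and remission comes at 1.5 months (both assumed), one-year mEFS would be at most 0.90 × exp(−0.50 × 10.5/12) = 58%.
- In that scenario the relapse hazards are identical. The 4-point excess in cumulative incidence arises only because fewer VEN + LDAC patients die first; it is not evidence of less durable remission.

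**Conclusion.** The point holds as a modest correction to a stated method. Following the text, 1-KM for morphological and molecular relapse overstates the proportion who relapse as soon as any patient dies in remission. Under constant hazards and the assumed ranges, the overstatement is about 0.2 to 4.6 points at 2 years. Whether it differs between arms, and in which direction, cannot be settled from the article. A gap of about 2 to 3 points would need net death without relapse of 5% versus 15–20% at 1-KM of 40%, and the gap is nil if death and relapse rates are equal. Only two secondary outcomes are touched. The primary mEFS analysis, the go rule, the 116 events and the 156 patients stand.

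**What to change.** Restrict the Kaplan-Meier sentence to mEFS and overall survival. For time to morphological relapse and time to molecular relapse, plot the Aalen-Johansen cumulative incidence by arm, with death without relapse as a competing event. Label the modelled hazard ratio for these two outcomes as cause-specific. It would help to report the cause-specific hazard ratio for death without relapse beside it, so that a difference in cumulative incidence can be traced to relapse or to death.

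The cost is a sentence or two in the analysis section and standard software. Deaths are already collected for overall survival, so no new data are needed and the sample size does not change.

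### For quality of life, performance status and geriatric assessment the stated analysis is descriptive only, which does not match the aim of showing greater benefit on secondary outcomes

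*Protocol article*

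**What the plan says.** The Statistical analysis plan section of the protocol article opens with two aims. The first is non-inferiority on mEFS. The second is to determine whether there is sufficient evidence "in addition that VEN + LDAC has greater benefit than IC in terms of secondary outcomes".

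Three of the secondary outcomes in the Trial outcomes section matter here. Quality of life is listed as "health-related quality of life at month 3, 6, 12, 18 and 24". Performance status is assessed at the same five visits, as a change from its starting value. The Comprehensive Geriatric Assessment (CGA) is likewise assessed as a change, "from baseline at month 12 and 24".

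The analysis section then states a general framework: "Outcome measures will be analysed under a Bayesian framework using conjugate models with minimally informative prior distributions". It goes on by type of outcome:

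- Time-to-event: a hazard ratio "estimated from the exponential of the mean of this distribution together with 80% and 95% credible intervals".
- Binary: "the difference in proportions will estimated together with 80% and 95% credible intervals".
- Total cost: an absolute difference in means between arms, with no interval stated.
- Quality of life, performance status and CGA: "Quality of life, change in performance status and change in CGA will be summarised and displayed graphically".

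**The concern.** The last item states a method, and that method stops short of a comparison. Summaries by arm and plots do not say how large the difference is or how certain one can be of its direction. For these three outcomes the second aim therefore has no stated analysis behind it.

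This matters more here than in many phase II trials. Quality of life is one of only two secondary outcomes named in the abstract. The Background puts forward the possibility that VEN + LDAC is at least as good on it. The Sample size determination section accepts a fall in one-year mEFS from 63% to 55%, and a critical hazard ratio above 1, because of the expected benefits to patients. If efficacy is traded for patient benefit, that benefit should be estimated with its uncertainty. The trial is also open-label and patients complete the questionnaires themselves. If curves are compared by eye, a reader can pick whichever visit or scale looks favourable.

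**Working it through.** **Plan's own figures.** The article gives no precision or power figure for these three outcomes. Its sample-size figures concern mEFS only, and they reproduce:

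- Margin: ln(0.55)/ln(0.63) = 1.294 (stated 1.29).
- Critical hazard ratio with 116 events: exp(ln 1.29 − 0.8416 × 2/√116) = 1.103 (stated 1.1).

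Neither bears on this point.

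**What each outcome yields if the text is followed**

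| Outcome | Between-arm estimate | Interval |
|---|---|---|
| Overall survival, times to relapse | hazard ratio | 80% and 95% |
| Early death, remission | difference in proportions | 80% and 95% |
| Total cost | absolute difference | none stated |
| Quality of life | none | none |
| Change in performance status | none | none |
| Change in CGA | none | none |

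The general Bayesian sentence does not fill the last three rows, because no model is named for a continuous, ordinal or repeated measure.

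**Would a contrast be informative at this size?** The figures below are illustrative. They treat the outcome as continuous with a flat prior and express differences in SD units, so they suit a quality-of-life score and not performance status.

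Inputs: 156 patients allocated 1:1 give 78 per arm. The share assessable at a visit is not stated. SE = √(1/n₁ + 1/n₂), and the interval half-width is 1.2816 × SE (80%) or 1.96 × SE (95%).

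- All 78 per arm: SE = √(2/78) = 0.160; half-widths 0.21 and 0.31 SD.
- 65 per arm (assumed): SE = √(2/65) = 0.175; half-widths 0.22 and 0.34 SD.
- Month 24: the article cites two-year overall survival of 50% for intensive treatment (Background) and 75% for venetoclax (Sample size determination). That leaves 78 × 0.50 = 39 and 78 × 0.75 ≈ 58 alive. SE = √(1/39 + 1/58) = 0.207; half-widths 0.27 and 0.41 SD, before any missing questionnaires.

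Adjusting for a baseline score correlated 0.5 with the outcome (assumed) would multiply the SE by √(1 − 0.25) = 0.866, giving 0.152 at 65 per arm. The Trial outcomes section does not say that quality of life is measured at baseline, so this gain is conditional.

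**In terms of the plan's 80% criterion.** The plan applies this threshold to mEFS only; it is borrowed here as a yardstick. For an assumed true benefit of 0.3 SD, the chance that the posterior probability of benefit reaches 80% is Φ(0.3/SE − 0.8416):

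- 65 per arm: Φ(1.710 − 0.842) = 81%.
- Month 24, 39 and 58 alive: Φ(1.449 − 0.842) = 73%.

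**Number of comparisons.** With, say, three quality-of-life scores at 5 visits, performance status at 5 and CGA at 2, there are 15 + 5 + 2 = 22 visit-level contrasts. With no true effect, each has a 20% chance of passing an 80% threshold, so about 22 × 0.20 = 4.4 would be expected to pass.

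**The case against.** Descriptive reporting of quality of life is acceptable in a phase II trial. The article presents the trial as a proof of concept, and its go decision rests on mEFS alone. That stands: description is not a fault in itself, and the defect is only that it does not match the stated aim.

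A reader might infer that the whole second aim cannot be answered. The documents do not support this. The aim does not require benefit on every secondary outcome, and overall survival, early death, remission and cost are all contrasted between arms.

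A reader might also fault the plan for giving no posterior probability of benefit on these outcomes. The article commits to such a probability only for mEFS, so its absence here is no inconsistency.

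It can be said that the sentence is condensed and that a fuller document supplies the contrast, since the general Bayesian statement makes no exception. That is possible, and the choice of scale and model terms is ordinary SAP content. But the article is not silent: it names description for these three outcomes directly after naming contrasts for others. If a fuller document does specify a contrast, the two texts need to be reconciled.

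Finally, a contrast brings difficulties of its own. There would be many visit-level comparisons, deaths would truncate quality of life and possibly differently by arm, performance status is ordinal, and CGA has several domains. Nor would an interval remove open-label reporting bias. These objections stand and shape the fix.

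**Conclusion.** The point holds in a limited form. For quality of life, change in performance status and change in CGA, the stated analysis gives no between-arm estimate or interval, although the section aims to establish greater benefit on secondary outcomes. The other secondary outcomes named above and the mEFS decision are not affected.

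The planned size would support a useful estimate for a continuous score: an SE of about 0.175 SD at 65 per arm and about 0.21 SD at month 24. These figures rest on an assumed number assessable, on survival figures the article takes from earlier data, and on a simple mean difference among survivors. They show feasibility and are not a forecast. In particular, the 81% chance at 65 per arm should not be carried to every visit; on the cited survival figures it is 73% at month 24, and lower once questionnaires are missing.

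**What to change.** Either of two changes removes the mismatch.

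**Option 1: add the comparison.** Replace the sentence on these three outcomes with wording along these lines:

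> Quality of life, change in performance status and change in CGA will be compared between arms, and the difference reported with 80% and 95% credible intervals. One quality-of-life scale at one time point is the lead comparison; other scales and visits are supportive. Analyses adjust for the baseline value where collected and for the randomisation factors. Performance status will be analysed by an ordinal or categorical method. Quality of life will be compared among patients alive at the visit and shown alongside survival.

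The text should also say which CGA score or domain is compared, because a single mean-difference model would not suit all three outcomes. The plots stay. When choosing the lead time point, the team should bear in mind that fewer patients are alive at later visits. The comparison among survivors is no longer fully protected by randomisation, which is why it belongs beside the survival results.

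**Option 2: narrow the aim.** Limit the second aim to the secondary outcomes that are formally compared, and label these three as descriptive.

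**Cost.** Option 1 needs modest extra analysis work, and the many visit-level results must be read as supportive. Option 2 needs wording only, but leaves the quality-of-life part of the rationale without an estimate. Neither needs new data or changes the mEFS decision rule.
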